##### Secondary outcomes

2.13.3.2

Attendance (number of training sessions) and adherence (active practice time) will each be categorized based on the prescribed dose achieved: low (<33 %), medium (33–66 %), and high (>66 %). Chi-square tests will compare the two groups' attendance distribution and adherence levels.

The analysis of other secondary outcomes will follow the same approach as the primary outcome, using LMM.

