### Objectives

1.1

The THRIVE-CP trial evaluates the effectiveness of incorporating Music Motion Feedback into home-based motor training for adolescents and young adults with CP compared to home-based motor training without Music Motion Feedback. We hypothesize that the Music Motion Feedback group will demonstrate greater improvements in real-world movement behavior, functional improvement, limb function, and perceived goal performance than the control group. Additionally, we expect the Music Motion Feedback group to attend and adhere more to the training program.

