### Individualized motor training programs

2.4

Participants in both groups will engage in home-based motor training grounded in principles of neural plasticity [[6], [7], [8]]. After informed consent, an experienced physical therapist ([name]) will develop an individualized motor training program with each participant. The process includes setting a long-term goal using the Canadian Occupational Performance Measure (described under tertiary outcomes), conducting neurological, biomechanical, and motor control assessments to identify specific movement limitations, and focusing on key factors for goal achievement. Short-term goals will be established following the SMART framework [18]. Participants will wear a small wireless IMU (MetaMotions from Mbientlab, San Francisco, United States) on the targeted body part during training (e.g., on the thigh for sit-to-stand), which will transmit movement signals via Bluetooth to a tablet's TIA app. IMU and tablet will be provided.

**Task-specific training** emphasizes meaningful, everyday activities, emphasizing neural plasticity's dependence on experience. Addressing each participant's unique challenges and goals is essential. Programs will foster intentional, active practice and minimize reliance on verbal or physical assistance, using visual cues to guide movement.

**Intensity** emphasizes high effort and challenging training to induce neuroplastic changes. It will be approached as a dynamic interplay between frequency, repetition, difficulty, resistance, session duration, and overall program length, recognizing that optimal learning occurs under conditions that do not yield peak performance [19]. The training setups will allow participants to perform independently and at their convenience throughout the day.

**Virtual conferences** will be conducted by licensed physical therapists trained in the THRIVE-CP protocol. Five sessions of approximately 30 min each will promote adherence to the program and optimize training intensity. Participants' skill acquisition, training tolerance, and short-term goals will be reviewed to either advance progression or address regression while maintaining a balance between task difficulty and performance.

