**Fig. 2 fig2:**
[figure not shown]
SPIRIT figure. Schedule of enrollment, interventions, and assessments. **Note:***t*_1_ baseline, *t*_2_ 12 weeks (primary endpoint), *t*_3_ 24 weeks, *t*_4_ 26 weeks. Gross Motor Functional Classification Scale-Expanded and Revised (GMFCS-E&R), Action Research Arm Test (ARAT), Gross Motor Function Measure-66 (GMFM-66), 6-min walk test (6MWT), Canadian Occupational Performance Measure (COPM). (a) Systematic inquiry of potential events during virtual conferences. (b) Data will be collected continuously through the TIA app. (c) Only the Music Motion feedback group can be tracked for staying at or above the intensity threshold. (d) Involves completing the participant's involvement in the trial, including final data review, administrative tasks, and confirming that all study procedures have been appropriately completed.

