#### Secondary outcomes

2.10.2

The secondary outcomes will evaluate changes in capacity and function. Participants will be split based on goal-directed training for upper or lower extremities. The effects of upper-extremity training will be assessed using the Action Research Arm Test (ARAT) total score, isometric arm strength, and maximum grip strength. For lower-extremity assessment, the Gross Motor Function Measure-66 (GMFM-66), isometric leg strength, and the 6-min walk test will be applied. In addition, attendance and adherence will be monitored as process measures.

**ARAT** consists of 19 items across four dimensions: grasp, grip, pinch, and gross arm movement. Each item is rated on a 4-point ordinal scale ranging from normal performance to inability to perform any part of the test. The maximum total score is 57 points, with higher scores indicating greater functioning [21].

A hand dynamometer will determine the percentage change in **maximum hand grip strength** (Jamar Technologies, Horsham, PA, USA). Participants will squeeze the device maximally. After one practice trial, three measurements will be taken, with rest periods. The highest value will be recorded as the maximum grip strength.

**GMFM-66** is a 66-item observational assessment divided into five dimensions: Lying and rolling, sitting, crawling and kneeling, standing, walking, running, and jumping. Each performance is rated on a 4-point ordinal scale: Does not initiate task, Initiates task (<10 %), Partially completes task (10–99 %), and Completes task (100 %). Calculations of GMFM-66 scores require the use of a computer program, Gross Motor Ability Estimator-3 (GMAE-3) [22].

**6MWT** measures submaximal aerobic and functional gait capacity. Able participants will walk 6 min on a 30-m walkway with the enclosed corridor length marked at every 3-m interval. Cones mark turnaround points. The total distance walked over the 6 min is used as the score [23].

**Isometric strength** will be assessed using handheld dynamometry by measuring maximal isometric force for muscle groups. Three measurements will be recorded with rest periods, and the highest value (kilogram force) per muscle group will be recorded as the maximum.

The TIA app will collect **attendance and adherence data**, which includes daily logins, session duration, and the time spent moving the targeted extremity.

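### Attendance and adherence are cut into three classes and compared by a chi-square test that ignores class order; the uncut percentage of dose would usually be the better scale

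*Protocol article*

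**What the plan says.** All references are to the protocol article.

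- **Objectives (1.1)** state a directional expectation: "we expect the Music Motion Feedback group to attend and adhere more to the training program".
- **Secondary outcomes (2.10.2)** describe the app data, "which includes daily logins, session duration, and the time spent moving the targeted extremity". The note to Fig. 2 adds: "Data will be collected continuously through the TIA app". The note to Fig. 1 says that attendance and adherence data are gathered on the tablet in both groups.
- **Secondary outcomes, analysis (2.13.3.2)** define attendance by sessions and adherence by active practice time. Each is then reduced to three classes: they "will each be categorized based on the prescribed dose achieved", with low below 33%, medium from 33% to 66% and high above 66%. The test is fixed as well: "Chi-square tests will compare the two groups' attendance distribution and adherence levels".
- The same section sends every other secondary outcome to the mixed model. Section 2.13.3 assigns non-parametric methods to ordinal data, and section 2.13.3.3 uses Mann-Whitney for the COPM.

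No reason is given for the cut points, and no comparison of the uncut values is planned.

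**The concern.** A count of sessions and a duration of practice carry much more information than membership of one of three bands. Someone at 34% of dose is treated like someone at 65%, and someone at 67% like someone at 100%. The chi-square test then also drops the order of the bands: relabelling low, medium and high in any order gives the same p-value. It answers whether the two distributions differ in any way, whereas the hypothesis is that one arm does more. It also gives no effect size in sessions, minutes or percent of dose.

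Adherence is central to the trial's rationale. The Background says it is unclear whether feedback works directly or through higher intensity and adherence, and the Discussion presents better adherence as a main promised benefit. A non-significant result from an inefficient test could be misread as showing that feedback does not change adherence.

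**Working it through.** **Inputs from the documents.** 58 analysed participants, so 29 per arm at 1:1; SMD 0.76; stated power 81.8% (2.13.2); cut points 33% and 66% (2.13.3.2).

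**Assumptions.** Two-sided alpha 0.05, which the sample-size section does not state. Mean percent of dose 50–75% with SD 20–25 points, because the documents give neither. A shift of 0.76 SD, used only as a benchmark: in the protocol it comes from a meta-analysis of recovery and motor learning and is not an adherence effect.

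**Step 1: reproduce the protocol's power figure.** The noncentrality is 0.76 × √(29/2) = 2.894.
- Normal approximation: Φ(2.894 − 1.960) = 0.825.
- Noncentral t with 56 df: 0.812.

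Both agree with 81.8%. This figure belongs to the trial's sample size; no power is claimed for attendance or adherence.

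**Step 2: the planned test by formula.** With equal arms of size n, Pearson's statistic on the 2 × 3 table has (2 − 1)(3 − 1) = 2 df and noncentrality λ = n Σ (p₁ − p₂)²/(p₁ + p₂). With a control mean of 50% and SD 25, a 0.76 SD shift gives class probabilities (low, medium, high) of 0.25, 0.49, 0.26 in control and 0.07, 0.38, 0.55 with feedback. Then

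λ = 29 × (0.18²/0.32 + 0.11²/0.87 + 0.29²/0.81) = 29 × (0.1012 + 0.0139 + 0.1038) = 6.35,

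and a noncentral chi-square with 2 df exceeds 5.99 with probability 0.61. Simulation gives 0.60.

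**Step 3: simulated power, normal dose, 29 per arm.** The mean is set either as the average of the two arms or as the control mean.

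| Mean, SD (%) | Mean refers to | Chi-square | Mann-Whitney | t-test |
|---|---|---|---|---|
| 50, 25 | average of arms | 63% | 78% | 81% |
| 60, 25 | average of arms | 61% | 79% | 81% |
| 75, 20 | average of arms | 48% | 78% | 80% |
| 50, 25 | control arm | 60% | 79% | 81% |
| 60, 25 | control arm | 55% | 78% | 81% |
| 75, 20 | control arm | 43% | 78% | 81% |

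An ordered trend test on the same three classes reaches 71% (control mean 50%, SD 25) and 67% (control mean 60%, SD 25), so it recovers part of the loss. Even with cuts placed at equal thirds, the chi-square test reaches only 62%, and it would need about 44 per arm to reach 81.8%.

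**Step 4: sparse cells.** With a control mean of 70% and SD 25, the low class has probability 0.07 in control and 0.01 with feedback. Its expected count per arm is 29 × (0.07 + 0.01)/2 = 1.2, well below 5. The Background cites self-reported adherence of 56–99% in home programmes, so crowding into the top class is plausible.

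**Step 5: a different shape.** Suppose participants cluster at 15%, 50% and 85% of dose (SD 8), with these shares in low/medium/high:

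| Control | Feedback | Chi-square | Mann-Whitney | t-test |
|---|---|---|---|---|
| 40/30/30 | 10/30/60 | 75% | 75% | 81% |
| 30/40/30 | 5/50/45 | 62% | 42% | 52% |
| 35/30/35 | 5/45/50 | 74% | 48% | 60% |

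In the last two rows feedback mainly rescues non-users, and the chi-square test does best. A second run gave the same ordering in those two rows (63% against 46% and 55%; 75% against 49% and 61%).

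**The case against.** The strongest reply is that the size of the loss rests on a chosen distribution. A normal percentage with a pure shift suits a t-test or Mann-Whitney, and home training may instead split into non-users, partial users and full users. This stands. Step 5 shows that the ranking can reverse, so a reader who infers that the planned test is the weakest available goes further than the evidence allows.

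It is also fair that 0.76 SD is not an adherence effect, that the trial was not sized on these measures, that chi-square on dose bands is a valid test, and that sparse cells can be handled by an exact test. The rule for ordinal data is not flatly broken either, since chi-square is nominally non-parametric.

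A reader might further infer bias from a moving denominator. At the virtual conferences, skill, training tolerance and short-term goals "will be reviewed to either advance progression or address regression", so a faster-progressing arm might look less adherent. The documents do not establish this. Section 2.13.3.2 does not say whether the prescribed dose is the baseline or the current one, a definition that can be left to the analysis plan, and section 2.4 does not say that progression raises the prescribed sessions or minutes.

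Finally, programmes are individualised, so raw sessions and minutes mix engagement with differences in prescription. That is a reason to keep percent of dose as the lead scale. It is no reason to cut it into bands.

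**Conclusion.** The point holds as a matter of efficiency and of fit to the hypothesis. The protocol itself fixes a three-class cut and an order-blind test for finely recorded measures with a directional expectation. If dose achieved is roughly normal and the arms differ by 0.76 SD, the planned test has about 43–63% power at 29 per arm, against about 78–82% on the uncut percentage. These figures rest on assumed means of 50–75%, SDs of 20–25 points and a borrowed effect size. Under strong clustering the disadvantage shrinks or reverses. Sparse cells are likely if most participants reach the top class; how often depends on a mean that the documents do not give.

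The change is worth making but is not critical: these are secondary process measures, and the primary analysis is not affected.

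**What to change.** Make the between-arm comparison on percent of prescribed sessions and percent of prescribed active practice time, uncut. Use a linear model, or Mann-Whitney if the data are skewed, and report an effect estimate with a 95% CI. Give raw sessions and minutes as supporting results. Keep low, medium and high as a descriptive table, or test those classes with a trend test that respects their order.

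The change uses the same data and can be written into the statistical analysis plan that section 2.13 announces. Its only downside is possibly lower power if engagement turns out to be strongly clustered.

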##### Tertiary outcomes

2.13.3.3

The Mann-Whitney *U* test will be employed to compare Canadian Occupational Performance Measure score changes between the two groups.

#### Missing data

2.13.4

To address dropouts and discontinuations, including participants who meet exclusion criteria during the trial, we will use multiple imputations to generate overall estimates and standard errors that account for the uncertainty associated with the imputation.

#### Sensitivity analysis

2.13.5

As an example, sensitivity analysis will evaluate whether the number of days since the most recent BoNT-A injection in targeted muscles affects the estimated treatment effect. For each assessment (T1, T2, T3), the days since the most recent BoNT-A injection in targeted muscles will be calculated and included as a covariate in the primary mixed-effects model. Additional sensitivity analyses will be pre-specified in the complete statistical analysis plan, which will be finalized and uploaded to ClinicalTrials.gov before the last participant's first visit.

### Patient and Public Involvement

2.14

Patient and Public Involvement (PPI) was integrated into the THRIVE-CP trial design to ensure it aligns with the needs and perspectives of the target population. [name], a young woman with lived experience of CP, contributed to identifying priority research questions and refining the protocol.

### Ethics

2.15

The project will be approved by the Danish Health Research Ethics Committee before recruitment and will adhere to the Declaration of Helsinki [26]. Written informed consent will be obtained from eligible individuals, emphasizing voluntary participation and the right to withdraw without consequences. Parental permission will be sought for individuals aged 15 to 17. Age-appropriate information will be provided to ensure understanding of the implications of participation. Since the interventions are tailored to individual needs, it is not feasible to provide specific details about them before enrollment, as confirmed by the ethics committee (Case No. G-25025924).

### Protocol amendments

2.16

Any protocol or statistical analysis plan amendments will be declared with reasons on ClinicalTrials.gov.

### Dissemination of results

2.17

Findings will be shared to inform clinical practice and future research regardless of outcomes. Results will be published in peer-reviewed journals and presented at conferences. Outreach will involve the CP Youth Clinic at Rigshospitalet, with potential collaboration with the National Association for Cerebral Palsy Denmark. We will prioritize accessible communication through PPI involvement. Updates will be provided to the trial funder; however, they will not affect the design, analysis, interpretation, or reporting.

## Discussion

3

Music Motion Feedback is a promising approach to improving movement behavior and functional improvement in adolescents and young adults with CP, potentially increasing activity and reducing disability. By providing real-time extrinsic feedback in tailored home-based training, we utilize established motor learning principles to enhance adherence and long-term outcomes. However, the THRIVE-CP trial faces generalizability limitations, such as recruiting intrinsically motivated participants and the bias of CP severity affecting participation, with 70 % of participants projected at GMFCS-E&R I-II. Additionally, those with lower technological literacy may struggle with adherence to the Music Motion Feedback. The trial lacks a usual care group due to recruitment constraints, limiting our ability to assess the separate effect of Music Motion Feedback. However, the TRIVE-CP trial addresses a critical challenge faced by adolescents and young adults with CP. If effective, this technology could provide an accessible and scalable method to enhance adherence to home-based motor training and foster meaningful progress in real-world movement behavior and functional abilities. The findings may significantly impact practice by promoting sustainable behavioral changes and improving the quality of life for individuals with CP.

## Trial registration

ClinicalTrials.gov, Version 1, NCT06962618, Registered May 2025.

## Data Availability

No data was used for the research described in the article.
